# Comparison of high-flow nasal cannula and conventional oxygen therapy for high-risk patients during bronchoscopy examination: protocol for a randomized controlled trial

**DOI:** 10.1186/s13063-022-07001-5

**Published:** 2023-01-05

**Keywords:** High-flow nasal cannula, Conventional oxygen therapy, Bronchoscopy examination, Hypoxia

## Abstract

**Introduction:**

High-flow nasal cannula (HFNC) has been proven to improve oxygenation and avoid intubation in hypoxemic patients. It has also been utilized during endoscopy examination to reduce the incidence of hypoxia. However, little is known about the effects of HFNC versus conventional oxygen therapy (COT) on oxygenation during bronchoscopy examination via nasal route; particularly, no study has compared the use of HFNC with that of COT at similar F_I_O_2_ for patients who have high-risk factors of desaturation during bronchoscopy examination.

**Methods and analysis:**

This randomized controlled trial will be implemented in four academic centers in China. Patients who have high-risk factors including hypoxemia, hypercapnia, morbid obesity, and narrow airway will be enrolled to use HFNC or COT during bronchoscopy examination. In the HFNC group, the initial gas flow will be set at 50 L/min with a fraction of inspired oxygen (F_I_O_2_) at 0.45, if the patient tolerates, the flow can be increased to 60L/min at most, while in the COT group, oxygen flow will be set at 6 L/min via a conventional nasal cannula. After 5 min pre-oxygenation, the bronchoscope will be inserted via the nasal route. Vital signs, oxygenation (SpO_2_), and transcutaneous CO_2_ (PtCO_2_) will be continuously monitored. The primary outcome is the incidence of hypoxemia, defined as SpO_2_ < 90% for 10 s during bronchoscopy examination, and secondary outcomes include the need for treatment escalation and adverse events.

**Discussion:**

Hypoxia is a common complication of bronchoscopy, our study attempted to demonstrate that HFNC may reduce the probability of hypoxia during bronchoscopy in high-risk patients. The results will be disseminated through peer-reviewed journals and national and international conferences.

**Trial registration:**

http://www.chictr.org.cn/: ChiCTR2100055038. Registered on 31 December 2021.

## Strengths and limitations of this study

### Strengths

➣ This is the first study to compare the utilization of HFNC with that of conventional nasal cannula at similar F_I_O_2_ during bronchoscopy examination via nasal route for patients who have high-risk factors➣ This is the first study to report the need for treatment escalation to resolve hypoxemia during bronchoscopy examination, of which the study findings have clinically meaningful implications➣ This is the first study to demonstrate the effects of HFNC on transcutaneous CO_2_ during bronchoscopy examination.

### Limitations

➣ The study enrolls patients with four different risk factors; the general conclusion might not apply to any specific group.➣ This study does not limit the procedures of bronchoscopy; the general conclusion might not apply to any specific procedure.➣ This study excludes critically ill patients, thus the findings may not apply to these patients

## Introduction

### Background

High-flow nasal cannula (HFNC) is an oxygen supply system that allows setting the gas flow and the fraction of inspired oxygen (F_I_O_2_) separately [1]. Because of its ability to provide high gas flow to exceed the inspiratory flow demand of patients, F_I_O_2_ is constant during HFNC treatment [2, 3]; moreover, the high flow also generates positive end-expiratory pressure [1, 4]. Therefore, HFNC has been proven to be superior to conventional oxygen therapy (COT) in improving oxygenation and avoiding intubation in hypoxemic patients [5–14]. Additionally, HFNC is also shown to reduce hypercapnia and improve ventilation in patients with chronic obstructive pulmonary disease (COPD) [15–21], since high-flow gas washes out the dead space [19–21].

In recent years, HFNC has been utilized to improve oxygenation or avoid desaturation during endoscopy examination [22–37], as hypoxemia is the most common complication during endoscopy examination, particularly with sedation [31–33, 38, 39]. The reported incidence of hypoxemia in the RCTs varied from 28.8 to 89.7% during flexible bronchoscopy examination [22–30]. Patients who require bronchoscopy examination may have existing pulmonary diseases, and the insertion of bronchoscope occludes part of the airway, resulting in increased respiratory resistance. Both factors may contribute to hypoxemia and hypercapnia during bronchoscopy examination [40–42].

Till now, seven randomized controlled trials (RCTs) have compared the use of HFNC with that of COT during bronchoscopy examination and found that the incidence of hypoxia was lower in the HFNC group [22–26, 29, 30]. Most of the RCTs [22, 25, 26, 29, 30] were implemented with bronchoscopy via the oral route, and during the examination, HFNC was utilized with the mouth constantly open, which might cause the significant loss of the benefits of HFNC in constant F_I_O_2_ and positive end-expiratory pressure. Nasal insertion of bronchoscope would allow patients to breathe with mouth closed, which might reserve the benefits of HFNC. Besides, nasal insertion of bronchoscope is more favorable in our institutions, because it causes fewer retch reflexes and enables better control during insertion as well as additional inspection of the nasal airway [42]. Nevertheless, little evidence is available to support the utilization of HFNC during bronchoscopy via nasal insertion. Therefore, we propose an RCT to compare the use of HFNC versus that of COT during bronchoscopy examination via nasal insertion among high-risk patients. Besides hypoxemic patients, we will also enroll three other types of patients as “high-risk” patients, including (1) patients of hypercapnia with chronic pulmonary disease, who might have increased CO_2_ and hypoxemia during bronchoscopy [40–42], (2) morbidly obese patients who were reported to experience hypoxemia during endoscopy examination [32], and (3) patients of narrow airway with radiology evidence prior to bronchoscopy [42, 43]. Our hypothesis is that the incidence of hypoxemia will be lower in the HFNC group than in the COT group during nasal bronchoscopy examination for patients with high-risk factors.

## Methods

This is a multi-center randomized controlled trial, which has been approved by the Ethic Committees of East Hospital (Shanghai, China) and Changhai Hospital (Shanghai, China). This trial is registered with Chictr.org.cn (ChiCTR2100055038). The report of the protocol followed the SPIRIT guideline [44].

### Study population

Patients who need bronchoscopy examination will be recruited from outpatient clinics or inpatient units in the four academic hospitals in China.

#### Inclusion criteria

Adult patients who have one of the following high-risk factors will be enrolled in the study: (1) hypoxemia with the PaO_2_/F_I_O_2_ ≤ 300 mmHg before bronchoscopy examination; (2) hypercapnia with PaCO_2_ ≥ 45 mmHg and baseline chronic pulmonary disease, including COPD, and bronchiectasis, etc.; (3) narrow trachea confirmed by radiology before bronchoscopy, which may have been caused by tracheomalacia, trachea tumor or granuloma, or aspirated foreign body, etc.; and (4) morbidly obese patients with body mass index (BMI) ≥ 30 kg/m^2^.

#### Exclusion criteria

Patients will be excluded if any of the following criteria is met: (1) refuse to participate; (2) local/general anesthesia bronchoscopy or rigid endoscopy is indicated; (3) age ≥ 90 years, or < 18 years; (4) pregnancy; (5) estimated duration of bronchoscopy is less than 10 min; (6) contraindication to using HFNC, including nasopharyngeal obstruction and blockage; (7) require oxygen flow ≥ 3L/min to maintain SpO_2_ at 90–97%; (8) central airway narrowness > 80%; and (9) the patient is critically ill and unsuitable for study inclusion assessed by anesthesiologists and pulmonologists.

### Study procedures

See the study diagram in Fig. 1.

**Fig. 1 Fig1:**
[figure not shown]
Study flowchart. Abbreviations: HFNC, high-flow nasal cannula; HR, heart rate; RR, respiratory rate; BP, blood pressure; SpO_2_, peripheral capillary oxygen saturation; PtCO_2_, percutaneous carbon dioxide; MV, mechanical ventilation. ^*^For HFNC group, increase F_I_O_2_ to 1.0; For COT group, change to HFNC at 60 L/min and F_I_O_2_ 0.45, if SpO_2_ cannot be maintained, increase F_I_O_2_ to 1.0

#### Recruiting and consent process

The nurse responsible for scheduling bronchoscopy examinations for patients in the bronchoscopy suite will screen the patients. The study investigator will be notified of eligible patients and will obtain informed consent from the patients. Study purposes, procedures, risks, and benefits will be discussed with the patients in a private room. Consent forms will be given to patients for full consideration before the examination day. On the examination day, arterial blood gas will be assessed for patients who are enrolled in the study due to hypoxemia and/or hypercapnia on the screen day. If the patients still meet the inclusion criteria and sign the consent form, they will be enrolled for randomization. Together with the other two types of patients (narrow airway and morbidly obese), they will be randomized to receive HFNC or COT during bronchoscopy examination after signing the consent form in the presence of the study investigator.

#### Bronchoscopy examination and hypoxemia management

Topical anesthesia will be provided prior to bronchoscopy as routine treatment. Sedation and/or anesthesia will be utilized by an anesthesiologist at the bedside. The depth of sedation will be assessed using the Modified Observer’s Assessment of Alertness/Sedation Scale(MOAA/S), and the score will be maintained at 2 ~ 3 throughout the examination process. The timing to use, the name, and the dose of sedation will be recorded. Bronchoscopy examination will be performed by experienced pulmonologists in the bronchoscopy suite. SpO_2_, PtCO_2_, and vital signs will be continuously monitored while F_I_O_2_ for HFNC and oxygen flow for COT will be maintained until the patients experience the first desaturation, defined as SpO_2_ ≤ 90% for 10 s. The timing and the lowest SpO_2_ in the first desaturation will be recorded (Fig. 1). Once desaturation occurs, jaw thrust maneuvers and/or suspension of bronchoscopy examination will be implemented to improve oxygenation. If desaturation persists, F_I_O_2_ will be increased to 1.0 in the HFNC group while in the COT group, COT will be changed to HFNC with flow at 60 L/min and initial F_I_O_2_ at 0.45, F_I_O_2_ will be increased to 1.0 if hypoxia remains. All the management will be recorded as treatment escalation. If SpO_2_ is still below the safe range, advanced airways, including nasopharyngeal airway, oropharyngeal airway, laryngeal mask, or tracheal intubation, will be inserted depending on patient situation (Fig. 1). The process, the duration, and the reason for the suspension of bronchoscopy examination will be recorded. After the recovery, whether bronchoscopy will be resumed or not will be determined by pulmonologists based on the clinical situation. Notably, besides desaturation, other adverse events may also cause the examination to be suspended, such as tachycardia, severe hypertension, arrhythmia, etc. These events will also be recorded in detail. The duration of the bronchoscopy examination refers to the time from the first entry into the nasal cavity to the end of the examination, as well as the time of per interruption will be precisely documented.

#### Termination criteria

Bronchoscopy examination will be terminated if any of the criteria is met: (1) any of the adverse events, including hemodynamic instability, cardiac arrest, massive bleeding, and pneumothorax is observed or reported, and (2) despite maximal oxygen delivery, SpO_2_ cannot be maintained at a level ≥ 90%.

All the rescue treatments and resuscitation equipment are prepared in the bronchoscopy suite. Any patient who experiences adverse events will be rested and monitored in the general unit, until the patient recovers.

#### Post bronchoscopy monitoring

After bronchoscopy, SpO_2_, PtCO_2_, and vital signs will be continuously monitored until the patients return to pre-bronchoscopy status or are stable. The recovery time and postoperative adverse reactions will be recorded as well. After the patients recover, patient comfort will be assessed. Lastly, we will also survey the anesthesiologists and pulmonologists on their satisfaction with the bronchoscopy examination.

### Outcomes

The primary outcome is to compare the incidence of desaturation which is defined as SpO_2_ < 90% between patients using HFNC and those using COT. The secondary outcomes include the timing of the appearance of the first desaturation (namely desaturation time), the lowest SpO_2_ and the highest PtCO_2_ during the entire bronchoscopy examination, the need for treatment escalation and airway management, the number and duration of bronchoscopy suspensions, the incidence of adverse events, and the recovery time between the two groups. A post hoc analysis will be performed to explore the risk factors of desaturations during bronchoscopy examination among high-risk patients.

### Sample size calculation (https://clincalc.com/stats/samplesize.aspx)

This study is a superiority study. While in the study [26] with a patient population close to our study during bronchoscopy examination, the incidence of desaturation of HFNC vs COT group was 13.3 vs 33.3%, respectively. However, this previous study only included hypoxemic patients while we will enroll other types of patients, so the incidence of hypoxemia in the HFNC group in their study might be higher than the incidence in ours. Thus, we assumed that when the maximal concentration of oxygen is provided by the two assigned devices, that is, when F_I_O_2_ is set at 1.0 for HFNC and oxygen flow at 6 L/min for COT, the probability of desaturation is 10% in the HFNC group and 30% in the COT group, respectively. According to statistical calculation, the sample size should be 124, with a confidence level (α) of 95%, power (1-ß) of 80%, and margin (Δ) of 0.2. Assuming a 20% dropout rate during the study, we set the final sample size to be 148. An interim analysis will be conducted once 50% of the sample size is reached.

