### Statistical analysis

Categorical variables, including the incidence of desaturation, treatment escalation, suspension or termination of bronchoscopy, etc., will be presented as percentages and analyzed by chi-square test. Continuous variables, including the desaturation time, recovery time, the lowest SpO_2_, the highest PtCO_2_, etc., will be presented as mean ± standard derivation (SD) or median and interquartile rage (IQR) and compared by independent *t*-test or Mann Whitney test, depending on the normality of distribution, which will be tested by the Kolmogorov–Smirnov test. A two-sided *P*-value of < 0.05 will be regarded as statistically significant for all tests. Data analysis will be conducted with SPSS software (SPSS 23.0; Chicago, IL).

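### The final sample size of 148 does not cover the stated 20% dropout: 124 evaluable patients would need 155 enrolled

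*Protocol article*

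**What the plan says.** The Sample size calculation section of the protocol article describes a superiority trial and assumes that "the probability of desaturation is 10% in the HFNC group and 30% in the COT group, respectively". With 80% power and a conventional 5% error rate (expressed there as a 95% confidence level), it concludes that "the sample size should be 124". It then makes one adjustment: "Assuming a 20% dropout rate during the study, we set the final sample size to be 148". The inflation formula is not shown, and the section gives the 20% no meaning other than a dropout rate. The Statistical analysis section names the chi-square test for categorical outcomes, including the incidence of desaturation, at a two-sided 0.05 level.

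**The concern.** A dropout rate is a share of the patients who enter the trial. To finish with a required number, that number is divided by one minus the rate. The step from 124 to 148 looks instead like a 20% mark-up on the required number, which gives a smaller total. If so, a trial that loses the 20% it plans for will finish with fewer evaluable patients than its own calculation demands. The final sample size, the dropout allowance and the power claim would then be inconsistent. The final number also sets the interim analysis, which is due at half the sample size.

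**Working it through.** **Inputs.** From the Sample size calculation section: 10% (HFNC) versus 30% (COT), 80% power, 5% error rate, 124 before dropout, 20% dropout, 148 final. From the Statistical analysis section: two-sided testing and the chi-square test. The article gives no allocation ratio, so 1:1 is assumed.

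**Step 1: reproduce 124.** Pooled two-proportion formula, no continuity correction, with mean rate 0.20:

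n per arm = [1.960 × √(2 × 0.20 × 0.80) + 0.842 × √(0.10 × 0.90 + 0.30 × 0.70)]² / 0.20²

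= [1.960 × 0.5657 + 0.842 × 0.5477]² / 0.04 = 61.6, rounded up to 62.

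Two arms give 124, an exact match. Other common variants give different totals: 98 (one-sided), 116 (one-sided with continuity correction), 144 (two-sided with continuity correction) and about 118 (unpooled or arcsine). So 124 is the evaluable number required, and the base calculation is sound.

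**Step 2: the dropout step.**

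| Calculation | Result |
|---|---|
| 124 / (1 − 0.20) | 155 |
| Per arm, 62 / 0.80 = 77.5, rounded up to 78 | 156 for equal arms |
| 124 × 1.20 | 148.8 |
| Stated in the plan | 148 |

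The stated figure is the third line, truncated. The multiplier of 1.2 is inferred, since the article does not print it. The next step does not depend on that inference.

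**Step 3: what 148 delivers.**

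- With 20% loss: 148 × 0.80 = 118.4, so about 118 evaluable, or 59 per arm. The requirement is 124, or 62 per arm.
- Largest loss that still leaves 124: 1 − 124/148 = 16.2%.
- Shortfall in enrolment: 155 − 148 = 7 patients (8 for equal arms), or 7/155 = 4.5%.

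**Step 4: power.** With the same pooled formula, power = Φ{[0.20 × √n − 1.960 × 0.5657] / 0.5477}:

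| Evaluable per arm | Pooled formula | Exact, chi-square uncorrected | Exact, chi-square with continuity correction |
|---|---|---|---|
| 62 | 80.3% | 81.0% | 74.9% |
| 59 | 78.2% | 80.5% | 72.0% |

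The exact columns come from enumerating all outcomes at 10% versus 30% with a two-sided 0.05 level.

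**The case against.** The strongest reply is that almost nothing is lost. The plan's test is the chi-square test, and its exact power without correction is 80.5% at 59 per arm, only about half a point below the 81.0% at 62. On that measure 80% is still met. This is correct, and it means that the statement of a missed 80% must be tied to the pooled normal formula. It does not rescue the sentence: the plan fixed its requirement at 124 evaluable patients using that formula, and 148 with 20% loss does not supply 124 under any power method. With a continuity correction, power is below 80% at both sizes, so in that case the dropout step is not the main cause.

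A second reply is that the 20% could be read as an allowance added to 124. The wording, a dropout rate during the study, does not favour that reading. Even on it, 148.8 should be rounded up to 149.

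A third reply is that the practical risk is low. Randomization takes place on the examination day and the primary outcome is observed during the same procedure, so a loss between 16.2% and 20% may well not occur. That is a fair point. It limits the importance of the error, but it is also a reason to state an allowance that the sample size supports.

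Finally, the uncertainty in the assumed rates, which were adjusted from 13.3% and 33.3% in one earlier study, matters more than 7 patients. This is true, but it is a separate matter from whether the arithmetic is right.

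**Conclusion.** The concern holds. Taking the 20% as the share of enrolled patients lost, and assuming 1:1 allocation, the plan needs 155 patients (156 for equal arms) and states 148. The stated number covers 16.2% dropout. At 20% it leaves about 118 evaluable patients, with 78.2% power by the formula that produces 124, against 80.3% at the required size. The loss is about 2 points by that formula and about half a point by exact calculation for the uncorrected chi-square test. The trial's validity is not threatened, but the final sample size and its dropout allowance are wrong as written and should be corrected.

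**What to change.** Keep 148 and replace the dropout sentence with one of these:

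- *A total of 148 patients allows for about 16% dropout while retaining the 124 evaluable patients required for 80% power.*
- *With 148 patients, 20% dropout would leave 118 evaluable patients and about 78% power (pooled two-proportion formula, 10% versus 30%, two-sided 0.05).*

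The second version should name the formula, because exact power of the uncorrected chi-square test is slightly higher. Either version costs one corrected figure that is slightly less favourable than the present text. It needs no extra patients, leaves the design and analysis unchanged, and leaves the interim point at 74 patients if half of 148 is meant.

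If the investigators truly expect 20% loss and want to keep 124 evaluable, the alternative is to enrol 155 (156 for equal arms), which is 7 or 8 more patients. Half of 156 would then move the interim point to 78.

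### The half-way interim has no stated purpose while 0.05 applies to every test: if desaturation is tested for efficacy there, the type I error is about 8.3%, not 5%

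*Protocol article*

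**What the plan says.** The sample size section of the protocol article assumes that "the probability of desaturation is 10% in the HFNC group and 30% in the COT group, respectively". It sets the design values "with a confidence level (α) of 95%, power (1-ß) of 80%, and margin (Δ) of 0.2" and concludes: "According to statistical calculation, the sample size should be 124". Dropout takes the total to 148. The section then ends with the article's only sentence on an interim: "An interim analysis will be conducted once 50% of the sample size is reached". That sentence names no endpoint, no comparison and no decision that could follow.

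The statistical analysis section assigns the incidence of desaturation, which is the primary outcome, to the chi-square test. It closes with the only significance rule in the article: "A two-sided *P*-value of < 0.05 will be regarded as statistically significant for all tests". No exception is made for an interim or a final look.

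**The concern.** The article plans two looks at the data, sizes the trial for one, and states a single threshold that it extends to every test. If the primary chi-square test is run at both looks under that threshold, there are two chances to cross 1.96, and the chance of a false claim of benefit is more than 5%.

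This could matter in practice. With half of 148 patients, 1:1, there are 37 per arm. At the assumed rates that means about 37 × 0.10 = 3.7 events against 37 × 0.30 = 11.1. If those rates are true, about 59% of trials would show P < 0.05 at that point. The investigators would then hold a nominally significant result at half the sample, in an open-label trial, with nothing in the article to say whether it counts.

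**Working it through.** **Inputs.** From the sample size section: rates 0.10 and 0.30, alpha 0.05, power 80%, total 124 before dropout and 148 after, one interim at 50%. From the statistical analysis section: chi-square test, two-sided 0.05. Assumed here, because the article does not state it: 1:1 allocation.

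**1. Reproduce the stated sample size.** With pooled variance and no continuity correction, the mean rate is 0.20 and

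n per arm = [1.960 × √(2 × 0.20 × 0.80) + 0.842 × √(0.10 × 0.90 + 0.30 × 0.70)]² / 0.20²
= (1.109 + 0.461)² / 0.04 = 2.464 / 0.04 = 61.6, so 62 per arm and 124 in total.

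This matches the article. It is a single-look calculation that uses the full 0.05 once.

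**2. Error of two looks at 0.05.** Under no difference, the interim and final statistics are approximately bivariate normal with correlation √0.5 = 0.707. Then

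overall error = 1 − P(|Z₁| < 1.96 and |Z₂| < 1.96) = 1 − 0.9169 = 0.0831.

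If the interim falls at 74 patients and the final test has only 124 evaluable patients (information fraction 74/124 = 0.597), the figure is 7.97%.

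**3. Check with the actual test.** Chi-square test without continuity correction, 0.05 at both looks, 2,000,000 simulated trials per setting:

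| Common event rate | Looks at 31 and 62 per arm | Looks at 37 and 74 per arm |
|---|---|---|
| 10% | 8.8% | 9.1% |
| 20% | 8.1% | 8.3% |
| 30% | 8.3% | 8.4–8.5% |

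The final test alone, with no claim possible at the interim, gives 5.0% to 5.1% at 74 per arm.

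**4. Thresholds that restore 5%.** O'Brien-Fleming-type alpha spending allots at half information 4 × [1 − Φ(2.2414/√0.5)] = 4 × 0.00076 = 0.003. A final threshold of 0.049 then gives an overall error of 5.00% by the formula in step 2. Other choices by the same formula:

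| Boundary | Interim P | Final P | Overall error |
|---|---|---|---|
| Classical O'Brien-Fleming | 0.0052 | 0.0480 | 5.00% |
| Pocock | 0.0294 | 0.0294 | 5.00% |
| Haybittle-Peto | 0.001 | 0.05 | 5.02% |

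**5. Cost in power.** At 10% against 30%, with looks at 31 and 62 per arm, simulated power is 81.1% with 0.003/0.049. A single test at 0.05 with 62 per arm gives 81.0%.

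**The case against.** A reader might infer that the trial, as planned, has an 8.3% false-positive rate. The documents do not support that. The interim sentence does not say that desaturation will be compared between arms, or that a result could be declared or could stop the trial. The statistical analysis section does not mention the interim. The article has no trial-level efficacy stopping rule; its termination criteria concern the individual examination. A look that is blinded or serves only safety or futility leaves the final test at its nominal level, as step 3 shows. This objection stands, and it makes the finding conditional.

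A second objection is that an article commonly leaves the purpose and boundaries of an interim to the full protocol or the analysis plan. It is also fair to say that the phrase on all tests closes a paragraph about outcome comparisons and need not have been written with the interim in mind. This stands in part: the absence of a boundary is not in itself a fault. But the article does more than stay silent. It states a threshold and extends it to all tests. An analysis plan that set an alpha-spending boundary would contradict that sentence, so the sentence would need correcting in that case too.

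**Conclusion.** The point holds in conditional form. One stated rule, 0.05 for all tests, sits beside a planned interim of unstated purpose and a sample size that spends the full 0.05 on one analysis. If desaturation is tested between arms at the interim and P < 0.05 there can be claimed, the overall two-sided type I error is about 8.3%, and 8.3% to 9.1% with the chi-square test at 37 then 74 per arm. If not, it stays at about 5%.

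The calculation is firm. Which case applies cannot be read from the article. The figures rest on 1:1 allocation, on the interim falling at half of 148, and on a final test at the full sample. The variants in steps 2 and 3, with 124 rather than 148 patients, stay between about 8.0% and 8.8%.

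**What to change.** Act before the half-way look, because a rule chosen after interim data are seen is not credible.

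- **State the purpose of the interim** in the article's sample size or statistical analysis section.
- **If it tests efficacy:** exempt the primary test from the blanket 0.05 rule and use an O'Brien-Fleming-type alpha-spending boundary. Efficacy is claimed at half-way only if P < 0.003, and the final test uses P < 0.049. If the look does not fall exactly at 50%, recompute both values from the same spending function.
- **If it does not test efficacy:** state that the primary outcome will not be tested for efficacy between arms at that look, and keep 0.05 at the end.

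The cost is about two sentences. With an efficacy look, the final threshold becomes 0.049 instead of 0.05, so a final P value between the two would no longer count as significant. Power stays at about 81% with 62 per arm, and no extra patients are needed.
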